#### System-level outcome measures

The health system-related outcomes recorded in this trial are:Minimum Processes of Care administered for each participant (including, e.g. use of interpreters, involvement of Aboriginal Liaison Officer, discharge plan involving family)Occasions of serviceResource utilisation using a purposefully designed questionnaire completed by each participant

These data are collected according to the schedule in Table 2 below:

**Table 2 Tab2:** Schedule for recording of system-level outcome measures

Data collection point (*time post-injury)*	Baseline (*0–6 weeks)*	1 (*12 weeks)*	2 (*26 weeks)*
Process of care indicators		X	X
Occasions of service		X	X
Resource utilisation		X	X

Resource utilisation will be used for the economic evaluation [16]

### Data management

Data collected during the trial will be recorded and stored using the RedCap™ [31] electronic data capturing tool. Additional data on outpatient use of allied health services during the trial period will be obtained from the Western Australia Department of Health (WA DoH). Data on inpatient use of allied health services during the trial will be obtained from the Allied Health System (AHS) where possible and manual extraction from medical files when not. In addition, data on Minimum Processes of Care will be extracted manually from files at the participating hospital sites. These data will be stored in comma separated values (csv) files, which will be merged with the trial data from RedCap™ [31] during analysis. All data and scripts generated for analysis will be archived and stored at the lead institution (Edith Cowan University) for a period of 7 years. Access to this data will be controlled by the lead chief investigator.

## Statistical analysis plan

### Analysis principles and general considerations

All outcomes and analyses were prospectively characterised as primary or secondary.This is a superiority trial with intervention expected to yield superior outcomes, compared to control. However, all outcomes will be tested independently at the two-tailed 5% significance level. All estimates of treatment effects will be presented with 95% confidence intervalsNo formal adjustments will be undertaken to constrain the Type I error associated with planned secondary or exploratory analyses. The information provided by analyses is designed to supplement the evidence from the primary analyses; it will provide a more complete characterisation of the treatment effects.The analyses for all quantitative outcome measures will be conducted on an intention the treat (ITT) basis, i.e. all participants will be analysed in the trial phase (control or intervention) in which they were recruited, regardless of whether their treatment adhered to the trial protocol or not. The ITT strategy for this trial is based on the following principles:◦ All available outcome data are collected on all recruited participant◦ For the ITT analysis, the outcomes for each participant will be included in the data for the trial phase (control/intervention) in which the participant was recruited.◦ All available outcome data will be used in the primary analyses. The primary analyses will be reported without imputation of missing data. If the amount of missing data exceeds 10% at the primary endpoint, missing data will be imputed under the assumption that data is missing at random.◦ A sensitivity analysis including all randomised individuals will be conducted. The sensitivity analysis will consider alternative assumptions about data missing not at random (MNAR).For primary and secondary analyses, the treatment effects for the participant-level effectiveness outcomes will be adjusted for brain injury type (stroke or TBI) and severity of injury (mRS) [18] at baseline. In addition, age at recruitment, timepoint (time since injury) and time period (6-month block of time in which the participant is recruited to the step-wedge trial) will be included as fixed effects. Hospital site will be included as a random effect. Unadjusted analyses will be reported separately from these pre-specified analyses.All analyses will be conducted using the R Statistical Programming Language [32] after data collection is completed and the database is locked.

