### Study design

Healing Right Way was planned as a stepped wedge trial with four steps over 3 years. Eight sites (four rural hospitals and four urban sites) are participating in the trial. The 3-year timeframe was divided into six 26-week periods. At the start of the trial, all sites were in the control condition which contributed a baseline measurement for all sites. The trial plan called for two sites cross over to the intervention condition, at the end of the first 26-week period, while the other sites remained in the control condition. At the end of the second 26-week period, two additional sites were to cross over from the control condition to the intervention condition, and at the end of the third 26-week period, the last two sites were to cross over to the intervention condition. Starting with the fifth 26-week period, all sites were to be in the intervention condition. The trial design allowed for one additional 26-week period in which all sites were to be in the intervention condition. We recruited fewer people than anticipated—especially in the initial periods after the trial commenced. The trial design was therefore modified to accommodate the reduced recruitment numbers. On advice of the Trial Management Committee, the trial design maintained four steps as planned, but the baseline extended period by an additional 26 weeks. The modified design is presented in Fig. 1.

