### Randomisation of sites

Since the rural sites are smaller in size and were expected to recruit fewer participants, a restricted randomisation strategy was considered appropriate. Moreover, due to differences in the availability of advanced care in the four rural sites, patients are often transferred from these sites to one of the urban sites. Therefore, for the purpose of randomisation, each rural site was paired with the urban site to which it usually transfers patients for acute care as needed. The four pairs formed by this process were treated as clusters for the purposes of randomisation. These clusters were designated as A, B, C or D by the trial data and operations manager. The trial statistician who was blinded to this designation, then generated the sequence in which the clusters would cross over to the intervention condition, using simple randomisation.

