### Sample size

Our sample size estimation procedure involved three steps. In the first step, we conducted a naïve sample size estimation which ignored the clustering effects of data collected through the stepped wedge design. In the second step, we calculated the design effect of the stepped wedge, using the method presented by Woertman et al. [27]. We then calculated the total sample size required by multiplying the naïve sample size calculated in the first step by the design effect and the total number of time periods in the planned design.

Our estimation was based on our primary outcome measure of Euro QOL–5D [17] VAS. We did not have any studies or preliminary data on the use of this measure in Aboriginal Australian populations. Therefore, our estimate of the effect of the intervention was based on the mean difference on the Euro QOL–5D [17] VAS between stroke and non-stroke populations in the published literature. Based on the literature [28, 29], the mean difference between stroke and non-stroke populations on the Euro QOL–5D [17] VAS was approximately 25 points with a standard deviation of 25. Guided by this information, we assumed that the intervention would result in an improvement of 15 points on the Euro QOL–5D [17] VAS (with a standard deviation 25), which equates to a standardised effect size of d = 0.6 for an independent sample t-test.

Using GPower 3.1 [30], we estimated the naïve sample size for an independent samples t-test and calculated that we would require a total of 90 participants to detect our estimated difference of d = 0.6 with 80% power at the 5% significance level.

The design effect proposed by Woertman et al. [27] is based on the number of clusters, number of steps, number of measurements at the end of each step and number of baseline measurements. Our proposed design had four clusters which were randomised to commence intervention in four steps, one baseline measurement and one measurement at the end of each step. We assumed a conservative intraclass correlation of 0.08. Based on these inputs, we calculated a design effect of 0.56. Multiplying the naïve sample size (n = 90) by the design effect (DEsw = 0.56) and the number of time periods in the trial (n = 24), and rounding-up our results to ensure that the number of patients per cluster per time period was an integer, we obtained a total sample size of 312 or 13 per cluster per time period.

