#### Analysis

A mixed effects linear regression model will be used to assess the between-group difference on Euro QOL–5D-3L [17] VAS score at 26 weeks post-injury. The model will control for injury type and severity (dichotomised mRS [18] at baseline), age at recruitment and time period (time since commencement of the trial) as fixed effects; recruitment site and participant/individual will be included as random effects. The treatment effect will be reported as the mean difference between the intervention condition and the control condition, together with the 95% confidence interval for the difference.

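### The models have no term for the four randomised site pairs, so the primary test and 95% CI are liable to be too optimistic if outcomes cluster by pair

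*SAP article*

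**What the plan says.** The trial has eight hospitals: "Eight sites (four rural hospitals and four urban sites) are participating in the trial". Under *Randomisation of sites*, "each rural site was paired with the urban site to which it usually transfers patients for acute care as needed". The same section then states: "The four pairs formed by this process were treated as clusters for the purposes of randomisation". The trial statistician "then generated the sequence in which the clusters would cross over to the intervention condition, using simple randomisation".

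The *Sample size* section uses the same unit: "Our proposed design had four clusters which were randomised to commence intervention in four steps". It adds: "We assumed a conservative intraclass correlation of 0.08".

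The analysis uses a different unit. The general principles say "Hospital site will be included as a random effect". For the primary model, "recruitment site and participant/individual will be included as random effects". The mixed models for the secondary outcomes repeat this structure. No model contains pair. The section on the effect of the lower sample size treats 108 participants as a convergence problem only. Its list of terms to remove starts with time period and ends with site.

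**The concern.** In a stepped wedge trial the treatment contrast inherits its randomisation from the units whose crossover date was drawn. Here those are four pairs. Two hospitals in a pair always cross over together, so anything they have in common in outcome or in drift over time moves with the treatment indicator. A site intercept treats the two as independent and counts that shared variation as if it came from separate units.

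The article itself gives a reason to expect shared variation, because pairs were built on the usual transfer route from rural to urban hospital. If it exists, the standard error of the treatment effect is too small and the single primary test rejects too often. A positive result from four randomised units would then be open to challenge. The secondary mixed models share the weakness.

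**Working it through.** **Inputs from the SAP article.** Four pairs, eight sites, simple randomisation of the order (*Randomisation of sites*, *Study design*); four clusters, ICC 0.08, 15 points with SD 25, naive total of 90, design effect 0.56, total of 312 (*Sample size*); two-tailed 5% (*Analysis principles*); 108 recruited (*Recruitment rate*).

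**Step 1: which unit does the plan's own figure use?** The two-sample t-test with d = 15/25 = 0.6, 80% power and two-sided 5% needs 44.6 per arm, so 90. The Woertman design effect with k = 4 steps, b = 1, t = 1, ρ = 0.08, n = 13 is

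[1 + ρ(ktn + bn − 1)] / [1 + ρ(ktn/2 + bn − 1)] × 3(1 − ρ) / [2t(k − 1/k)]
= (1 + 0.08 × 64)/(1 + 0.08 × 38) × 2.76/7.5
= 6.12/4.04 × 0.368 = 0.557, which rounds to 0.56.

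Then 90 × 0.56 × 6 periods = 302.4. Spread over 4 clusters × 6 periods = 24 cells, this is 12.6, rounded up to 13, and 13 × 24 = 312. The figure reproduces, and the cluster in it is the pair. The analysis model's cluster is the site.

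**Step 2: type I error of the planned structure.** I simulated trials with no treatment effect: 108 participants, eight sites in four pairs, six periods of which two are baseline, total variance 1, REML, fixed period effects and three covariates. There were 1,500 runs per scenario (Monte Carlo SE about 0.6 points). Assumptions not in the article: 3:1 urban to rural recruitment, recruitment rising over time, one 26-week value per participant, the split of the ICC, and the reference distribution. Rejection rates (%), nominal 5%:

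| Clustering | Site only, z | Site only, t on 7 df | Random pair + site, z | Random pair + pair-by-period, z | Permutation, 24 orders |
|---|---|---|---|---|---|
| none | 4.3 | 1.5 | 4.3 | 3.8 | 4.0 |
| 0.08 site | 6.4 | 2.3 | 6.2 | 6.2 | 4.0 |
| 0.04 pair, 0.04 site | 6.2 | 2.9 | 5.3 | 5.8 | 4.0 |
| 0.08 pair | 7.7 | 3.3 | 6.5 | 5.9 | 4.0 |
| 0.064 pair, 0.016 pair-by-period | 8.5 | 4.0 | 7.4 | 6.6 | 4.0 |
| 0.04 pair, 0.04 pair-by-period | 8.3 | 4.1 | 8.1 | 6.3 | 3.8 |
| 0.20 pair | 8.5 | 3.7 | 6.4 | 5.9 | 4.0 |
| 0.10 pair, 0.10 pair-by-period | 13.3 | 7.5 | 12.5 | 8.7 | 3.6 |

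With 0.08 all at pair, the mean model SE is 0.315 SD against a true SD of the estimate of 0.347. The ratio is 0.91, so the SE is about 9% too small: 0.315 × 25 = 7.9 against 0.347 × 25 = 8.7 VAS points. Coverage is 100 − 7.7 = 92.3%.

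**Step 3: pair as a fixed effect.** A second set (about 2,480 trials per scenario, N = 100-108) compared site only with z against pair fixed with a t reference:

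| Clustering | Site only, z | Pair fixed, t |
|---|---|---|
| 0.08 site | 6.6 | 5.0 |
| 0.04 pair, 0.04 site | 7.2 | 5.3 |
| 0.08 pair | 8.1 | 5.0 |
| 0.03 pair, 0.03 site, 0.02 pair-by-period | 8.5 | 5.6 |
| 0.04 pair, 0.04 pair-by-period | 9.8 | 7.2 |

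A further set gave 6.8% (all at site), 8.5% (all at pair) and 10.2% (with a pair-by-period part) for site only with z. With pair fixed, the first two fell to about 5.5% and the third to about 8%.

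**Step 4: which change does the work?** The comparison in Step 3 alters both the pair term and the reference distribution. A set of 3,000 runs with 0.08 all at pair separates them. Site only with z gives 9.1%. Satterthwaite degrees of freedom on that same model give 8.7%. Pair fixed with plain z gives 5.8%. The omitted pair effect is the main driver.

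**Step 5: the randomisation distribution.** Four clusters have 4! = 24 orders, so the smallest attainable permutation p is 1/24 = 0.042.

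**The case against.** A reader might infer that the plan's p-values and intervals are certainly too optimistic. The article does not support that. It gives one ICC and does not say how it divides between pair, site and pair-by-period. With no clustering the planned model gave 4.3% in one simulation set and 5.6% in another. With all of it at site the excess is small (6.3-6.8%). The rates near 10% need pair-by-period variation, which the article never mentions.

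A reader might also infer that the SAP plans large-sample Wald intervals. It does not say so. It promises a 95% CI and names R, and a condensed article commonly leaves the degrees-of-freedom method to a fuller plan. With t on 7 df the site-only model was conservative in every scenario except the most extreme (7.5%). So the unstated reference distribution calls for clarification and is not itself an error. The choice does matter: the critical value is 1.96 for z, 2.36 on 7 df and 3.18 on 3 df.

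Nor does the article say that paired hospitals exchange patients. It describes transfer from the rural to the urban site, which is one direction.

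Finally, a pair term is not a complete cure, since rates of about 7-8% remain where pairs drift differently over time. It also adds parameters to models that the authors already fear may not converge.

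All of this limits size and certainty. It does not answer the main point: the article spells out its random effects, and the unit it randomised and powered on is not among the model terms.

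**Conclusion.** The point holds in a limited form. Four pairs were randomised and used for the sample size, eight sites are modelled, and pair appears in no model. If part of the clustering lies at pair level, the primary test and 95% CI are liable to be too optimistic. Simulated type I error is about 6-9% at total ICC 0.08 without pair-by-period variation, and up to about 10% with it; only a more extreme assumed total of 0.20, half of it pair-by-period, reached 13.3%. These rates rest on a z reference and an assumed ICC split and recruitment pattern. The inflation is modest, and it comes mainly from the missing pair effect.

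**What to change.** Before analysis:

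- Include the randomised pair as a fixed effect (3 df), with site within pair as a random effect, in the primary model and the secondary mixed models.
- In the section on the effect of the lower sample size, keep pair and time period out of the list of terms removed on non-convergence. As written, time period goes first although condition is tied to calendar time by design, and removing site last would leave no clustering term above the participant.
- Name a small-sample method, Kenward-Roger or Satterthwaite, for the linear models. On its own this does little (9.1% to 8.7% in Step 4), so it does not replace the pair term.
- As sensitivity analyses, add a pair-by-period random term and report a permutation test over the 24 crossover orders. State that its smallest attainable p is 0.042, so it falls below 0.05 only when the actual order is the single most extreme one.

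The work is SAP wording and standard R packages. The statistical cost is wider intervals and lower power: for a 15-point effect, simulated power falls from about 43-50% to 34-40%. Part of that loss was false-positive inflation.

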
### Interim analysis

No interim analyses were planned for this trial. The Data and Safety Monitoring Committee (DSMC) reviewed safety and effectiveness data during the course of the trial. Due to the sequential nature of the trial (control condition precedes intervention condition at each site), there were no formal stopping conditions for effectiveness. The DSMC was guided by the Haybittle-Peto boundaries [33] in assessing safety concerns. That is, they could have recommended stopping of the trial if the number of serious adverse events (SAEs) in the intervention condition exceeded the number of SAEs in the control condition by at least 3 standard errors.

### Trial profile

The trial will be reported in accordance with the CONSORT extension for stepped wedge cluster randomised trials [23]. A CONSORT Flow Diagram will depict the total number of people screened for the trial and reasons for exclusion. Numbers related to withdrawal/loss to follow-up will be included in the diagram, with reasons detailed in text form.

### Demographics and baseline characteristics

Participant demographic and baseline clinical characteristics will be reported for participants recruited in each condition (control or intervention). Demographic characteristics will include age at recruitment, gender, recruitment region (metropolitan vs regional), place of residence (urban area, inner regional, outer regional, remote, very remote as per the Accessibility/Remoteness Index of Australia ARIA +) [34] and living arrangements prior to hospital admission. Baseline clinical characteristics will include injury type, injury severity (GCS [26] for TBI, NIHSS [25] for stroke and mRS [18] for all), HADS [21], FIM [19], history of alcohol consumption and drug use. Comorbidities/risk factors such as diabetes, renal and heart disease will be included. Categorical variables will be summarised using frequencies and percentages. Unless otherwise indicated in the tables, percentages will be based on the number of patients for whom data are available. Continuous variables will be summarised by the mean and standard deviation (SD) or by the median and interquartile range (IQR). The format for presentation of this data is outlined in Table 3 of Appendix.

### Adherence to intervention protocol

The number and percentage of participants who received the services of the ABIC will be reported. In addition, the number and percentage of participants who received the minimum number of ABIC visits (six visits on a monthly basis) as recommended in the protocol will be reported. In terms of the ABIC service, the per protocol groups will be formed based on whether participants adhered to the stated protocol or not—those who received the minimum amount of intervention will be included in the intervention group and those who did not receive the stated minimum amount of intervention, will be included in the control group. All hypotheses will be re-tested using the same models and standards as stated for the ITT analysis. The cultural security training will be reported in terms of a simple statement of the number of sites which received the required training.

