### The intervention

The trial implemented a complex intervention consisting of cultural security training for hospital staff and the employment of Aboriginal Brain Injury Coordinators (ABIC) to see the participants in hospital and up until 26 weeks post-injury onset and provide education, support, liaison and advocacy services to the participants and their families. The cultural security training involved workshops training 20 health professionals at each site (nursing, medical and allied health staff). The workshops were offered every 6 months during the intervention period for the site and consisted of a 3-h face to face component and 3 h of online modules. The Aboriginal Brain Injury Coordinator component required the Coordinator to be in contact with the participant a minimum of six times following their injury on a monthly basis during the intervention period.

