#### Stroke disability/injury severity

The score on the mRS [18] will be dichotomised as independent (mRS [18] 0–2) or dependent /dead (mRS [18] 3–6). A mixed effects logistic regression model will be used to assess between-condition differences on this binary variable. Time period, age at recruitment, injury type and severity (dichotomised mRS [18] at baseline) will be controlled for as fixed effects in the model. Recruitment site and participant/individual will be included as random effects. In addition, time since injury and the interaction of time since injury with condition (control/intervention) will be included in the model. The interaction effect will be used to assess the between-group differences at 12 weeks post-injury [H4.1] and at 26 weeks post-injury [H4.2].

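### The per-protocol rule moves intervention-phase participants with fewer than six coordinator visits into control: an as-treated regrouping that can create a false benefit or dilute a real one

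*SAP article*

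**What the plan says.** The main analysis follows recruitment phase: "all participants will be analysed in the trial phase (control or intervention) in which they were recruited" (Analysis principles and general considerations). The section Adherence to intervention protocol then sets up a second grouping. On one side, "those who received the minimum amount of intervention will be included in the intervention group"; on the other, "those who did not receive the stated minimum amount of intervention, will be included in the control group". The threshold is the "minimum number of ABIC visits (six visits on a monthly basis"), matching the section on the intervention, which asks for contact a "minimum of six times following their injury on a monthly basis during the intervention period". The scope is total: "All hypotheses will be re-tested using the same models and standards as stated for the ITT analysis".

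Two other statements bear on the rule. The intervention has two parts, a "complex intervention consisting of cultural security training for hospital staff and the employment of Aboriginal Brain Injury Coordinators (ABIC"), so staff training can reach an intervention-phase participant whatever the number of visits. And death is a scored state of the disability outcome: "The score on the mRS [18] will be dichotomised as independent (mRS [18] 0–2) or dependent /dead (mRS [18] 3–6").

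**The concern.** A per-protocol set normally drops participants who departed from protocol. This rule relabels them. Someone recruited at a trained hospital who had five coordinator visits is analysed as usual care. Three things follow.

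- **Allocation is lost.** Group membership no longer depends on the randomised crossover time but on something that happened to the participant after recruitment.
- **Control is contaminated.** It holds people exposed to trained staff and to part of the coordinator service. This is plainest for processes of care, which are extracted from hospital files and which the training is meant to change.
- **The label looks ahead.** Groups for 12-week outcomes are defined by visits that take place later, and reaching the sixth visit requires being alive and in contact for most of the follow-up.

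Recruitment reached 108 against a target of 312, so an inconclusive ITT result is a real possibility. A per-protocol result of uncertain meaning would then stand beside it for the primary and all 14 secondary hypotheses. The section does not itself call the re-test supportive.

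**Working it through.** **Yardstick.** The SAP gives no figure for the per-protocol analysis. Its design effect is 15 VAS points with SD 25, so d = 15/25 = 0.6. The noncentral t at two-sided 5% needs 45 per group, 90 in total (power 0.804), as the Sample size section states. Biases below can be read against 15 points.

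**Timing.** At 4-week spacing six visits span 5 × 4 = 20 weeks. Even a participant first seen on the day of injury has had at most four visits by week 12 (weeks 0, 4, 8, 12). The seven 12-week hypotheses (H2.1, H3.1, H4.1, H4.3, H5.1, H5.3, H5.5) are therefore re-tested on labels fixed after the outcome.

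**VAS, no true effect.** Assumptions, since the SAP gives no data on them: a share p of intervention-phase participants miss the minimum; g is the VAS gap (adherers minus non-adherers) left after covariate adjustment; the phases are equal (54 each).

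- Adherers lie pg above the phase mean, and non-adherers (1−p)g below it.
- Rule as written: bias = 2pg/(1+p).
- Excluding non-adherers instead: bias = pg.

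Example with p = 0.3, g = 10 and phase mean 60: adherers 63, non-adherers 53. Control becomes (54×60 + 16.2×53)/70.2 = 58.4, and 63 − 58.4 = +4.6. Exclusion gives 63 − 60 = +3.0.

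| p | g | as written | excluded |
|---|---|---|---|
| 20% | 5 | 2/1.2 = +1.7 | +1.0 |
| 30% | 10 | 6/1.3 = +4.6 | +3.0 |
| 40% | 10 | 8/1.4 = +5.7 | +4.0 |
| 50% | 15 | 15/1.5 = +10.0 | +7.5 |
| any | 0 | 0 | 0 |
| 40% | −10 | −8/1.4 = −5.7 | −4.0 |

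Unequal phases change this moderately. With control-to-intervention ratio r the bias is pg(r+1)/(r+p). For p = 0.3 and g = 10 that is 3 × 1.5/0.8 = 5.6 at r = 0.5 and 3 × 3/2.3 = 3.9 at r = 2.

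**VAS in a stepped-wedge model.** Simulation of 108 participants in four clusters and six periods (assumed: two baseline, four steps), SD 25, ICC 0.08, fixed periods, random cluster, 1,000 runs, p = 40%, no true effect:

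- g = 5, 10, 15: bias +4.0, +7.9, +11.7, with false claims of benefit in 9%, 21% and 41% of trials.
- ITT by phase: about 0, with 2–3%.
- Exclusion: +2.3, +4.2, +5.8, with 4%, 6% and 9%.
- g = −10: −7.6 under the rule as written.

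The bias exceeds the simple formula because period adjustment compares adherers with non-adherers recruited in the same period.

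**Dilution.** Suppose every intervention-phase participant gains 15 points and g = 0. The rule as written gives 15/(1+p) = 15/1.4 = 10.7 at p = 40%, and 5.8 in the simulated model. If non-adherers gain half, the simulation gives 10.2 against 11.7 for ITT.

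**mRS at 26 weeks, no true effect.** Assumptions: a share m of each phase dies before the sixth visit could be made; 60% of survivors are independent; a share q of survivors reach six visits, unrelated to prognosis. Adherers are 60% independent. The regrouped control proportion is 0.6(1−m)(2−q) / [1 + m + (1−m)(1−q)].

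- m = 5%, q = 0.6: 0.798/1.43 = 55.8%, spurious gain 4.2 percentage points; q = 0.8: 4.8.
- m = 10%: 8.2 and 9.4.
- m = 15%: 12.1 and 13.6.

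Exclusion compares 60% with 0.6(1−m), leaving 0.6m: 3, 6 and 9 percentage points.

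**The case against.** The strongest reply is that the primary analysis is ITT by recruitment phase and that the analysis principles present further analyses as supplementing it. That is correct, and it limits how serious the point is.

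A reader might infer that the rule manufactures a benefit. The documents do not support that as a general statement. For the VAS a false gain needs worse prognosis among low-contact participants beyond what baseline mRS, injury type and age explain, and the SAP reports neither adherence nor prognosis by adherence. Coordinator services could be given by telephone and telehealth, so illness or distance need not prevent contact, and sicker participants may have been contacted more. Nor does the death argument carry over to the VAS: the SAP assigns no VAS value to death and runs the primary model without imputation, so relabelled deaths add no low scores there.

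A reader might also infer that the six-visit minimum conflicts with recruitment up to week 6. The latest recruit has 26 − 6 = 20 weeks. Six visits at calendar months span 5 × 4.35 = 21.7 weeks, but at 4-week spacing they span exactly 20. The SAP says only that contact is monthly, so timing is tight for the latest recruits but the passages do not contradict each other.

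Finally, exclusion does not cure the selection problem; the figures above bear this out. What remains untouched by all of this is the relabelling itself: the text is explicit, nothing else in the SAP corrects it, and the resulting contrast has no clear interpretation in either direction.

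**Conclusion.** The point holds as a flaw in a supportive analysis and should be fixed; it does not threaten the primary result. The defect in the rule is certain from the text. The size of its effect is not.

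- **mRS:** an upward component is built in whenever an intervention-phase participant dies before the sixth visit: roughly 4 to 14 percentage points for early mortality of 5–15%, under the assumed 60% independence in survivors.
- **VAS:** direction and size turn on the assumed residual gap. The simple range reaches two thirds of the design effect at its upper end (10/15); the bias vanishes without a gap and reverses with an opposite one.
- **A real effect:** it can be understated, because exposed participants sit in the comparator.

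Adherence, prognostic gap, mortality, phase sizes and the period layout are all assumptions. The simulation adjusts for period and cluster only, so its gaps must be read as those left after covariate adjustment.

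**What to change.** Replace the grouping sentence with wording to this effect: the per-protocol set comprises all control-phase participants and those intervention-phase participants who met the stated minimum; intervention-phase participants below it are excluded, and no participant is analysed in a phase other than that of recruitment. Then:

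- Fit the same model as for ITT, adding baseline predictors of adherence that were measured, and name them in advance. Keep the list short, since the SAP already expects convergence problems.
- Label the analysis exploratory.
- State that exclusion reduces but does not remove selection bias, notably for mRS (early deaths leave only the intervention side) and for 12-week outcomes (selection still uses later visits).

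A complier-average estimate with recruitment phase as instrument is an optional companion. It needs the caveat that staff training reaches non-compliers: if everyone gained 15 points and 60% reached the minimum, it would return 15/0.6 = 25.

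The cost is SAP wording and a smaller set. At 30% non-adherence and 54 per phase, about 16 participants drop out, leaving about 92 of 108. No new data are needed.
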